### Outcome assessment

The study’s primary outcome measure is the OSS with the outcome at 4 months as the result of primary interest. Secondary outcomes are the results on the OSS at the other points of follow-up, results of the other study scores at all points of follow-up and the number of patients in each treatment group who change treatment during the study.

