### Change of treatment

Patients who are still symptomatic or have redeveloped symptoms at four month follow-up or later, will be considered for supplementary treatment measures by the blinded follow-up assessor. If necessary, they will be offered treatment as usual, which means barbotage (repeated barbotage if barbotage was the primary treatment), steroid injection (repeated injection if injection was the primary treatment), ESWT, surgery, or therapist guided physiotherapy treatment, depending on findings and patient preferences. Earlier re-examination and change of treatment can be considered, in accordance with the Helsinki Declaration, for patients who are symptomatic to an extent that they cannot wait until the four month control. Patients who change the treatment during follow-up will remain in the study and will be followed-up according to an intention-to-treat principle. Unblinding of patients in conjunction with a change of treatment, will only be performed if the patient explicitly insists on knowing his primary treatment selection.

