### Sample size

Calculation of sample size was performed for an ANOVA of our primary outcome, which is the result on the OSS at 4 month follow-up. To detect a minimally important difference of 4 (SD 7) points [26] with a power of 90%, a 2-sided significance level of 0.05, 60 patients are required in each treatment group. To compensate for expected 15% drop-outs, we plan to include 70 patients in each treatment group. A supplementary analysis showed that this sample size also will be sufficient for pairwise post hoc *t*-test analyses (1 versus 2, 2 versus 3 and 1 versus 3), still with a significance level after Bonferroni correction of 0.017 but with a power of approximately 80%.

The actual statistical analysis of the interventions on primary outcome will be conducted using linear mixed models for repeated measurements adjusted for outcome measure at baseline. It is expected to give a slightly higher statistical power than an ANOVA.

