### Statistical analysis

Demographic baseline data will be expressed for categorical variables as number of cases and for continuous variables by means with SD (if normally distributed) or by medians with range (if not normally distributed).

A linear mixed model for repeated measurements will be used for analysis. Because of an expected large number of crossovers after 4 months, the primary analysis will be performed on results up to 4 month follow-up and a secondary analysis on results up to 24 month follow-up. Analyses will be performed adjusted for baseline differences of the OSS and according to intention-to-treat. The linear mixed model will be estimated using linear maximum likelihood and include a random intercept, measure of the OSS at baseline as a covariate and observation time after intervention and type of intervention as factors. Mean differences (95% CI) between groups at 4 months follow-up will be presented from the linear mixed model to assess difference between interventions. A 2-sided *p*-value ≤ 0.05 is considered significant. Post-hoc pairwise comparisons for the primary outcome will be performed with p-value adjustments according to Bonferroni. Missing values will be handled by using mixed model analysis. Supplementary per-protocol analyses will be performed. A similar statistical analysis as described for the OSS will be used for the continuous secondary outcomes (QuickDASH, EQ-5D-5L).

Categorical variables will be expressed as numbers and percentages, and differences between groups will be analysed by the Chi^2^ or Fisher’s exact test. Possible associations between categorical baseline variables and outcomes will be explored by logistic regression analysis.

All subgroup analyses will be exploratory in nature and are planned for the size of the calcification at baseline (≤12.5 mm versus >12.5 mm), the volume of the removed material (≤0.1 ml versus > 0.1 ml), and the results on the Stanford expectation of treatment scale (positive expectancies versus negative expectancies). Selection of the threshold values for the size of the calcification at baseline and for the volume of the removed material are based on the findings of an unpublished pilot study from our institution.

Clinical safety will be investigated by assessing adverse events in a descriptive manner.

The statistician responsible for data analyses will blinded from the treatment allocation until completion of analyses.

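### The count of patients who change treatment is compared by a simple proportion test that takes no account of incomplete follow-up; time to first change would be a cheap, minor improvement

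*Protocol article*

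**What the plan says.** All references are to the protocol article.

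- **Outcome assessment** defines the outcome as "the number of patients in each treatment group who change treatment during the study". It gives no denominator and no event time.
- **Statistical analysis** has one rule that fits such an outcome: "Categorical variables will be expressed as numbers and percentages, and differences between groups will be analysed by the Chi^2^ or Fisher’s exact test". The rule is general and does not name this outcome.
- **Statistical analysis** also says "Missing values will be handled by using mixed model analysis". The mixed model is described for the OSS and the continuous secondary scores, so it does not reach a yes/no outcome.
- **Change of treatment** sets when a change normally arises: "Patients who are still symptomatic or have redeveloped symptoms at four month follow-up or later, will be considered for supplementary treatment measures". Earlier change is allowed for patients who cannot wait. Patients who change stay in follow-up.
- **Sample size** expects incomplete follow-up: "To compensate for expected 15% drop-outs, we plan to include 70 patients in each treatment group". The allowance belongs to the 4-month OSS. Neither the timing of the losses nor a 24-month figure is given.

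**The concern.** A change of treatment can occur at any time over 24 months, and it is seen only while the patient is in contact with the trial. A patient who leaves at month 3 without a change has an unknown status, not a negative one. A two-way table forces a choice: count that patient as unchanged, leave the patient out, or restrict the table to completers. The article does not say which, and the choices give different percentages. The table also treats a patient who could not wait for the 4-month visit like one who changes at month 20.

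This outcome shows how often the allocated treatment was not enough, and the analysis section itself expects many crossovers after 4 months. Understated percentages would make every arm look more successful than it was. If the arms lost patients at different rates, the comparison between them could be distorted as well.

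**Working it through.** **The plan's own figure.** 60 / (1 − 0.15) = 70.6, and 70 × 0.85 = 59.5. The 70 per arm agrees with 60 evaluable and 15% drop-out to within rounding. The plan gives no figure for the change rate itself.

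**Inputs.** From the documents: d = 0.15 drop-out, 70 per arm, changes mostly from month 4, follow-up to month 24. Assumed: a true 24-month change proportion p = 0.40; half of changes at month 4 and the rest even over months 4–24; none before month 4; drop-out unrelated to change.

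**Formulas.** Let m be the probability that drop-out comes before the change, in a patient who would do both.

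- All randomised: p(1 − dm), so the relative shortfall is dm.
- Known status (completers plus drop-outs already seen to change): p(1 − dm) / [(1 − d) + dp(1 − m)].
- Completers only: p.

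**Values of m.**

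- All drop-outs leave before month 4: m = 1.
- Drop-out even over months 0–24: m = 0.5 × 4/24 + 0.5 × 14/24 = 0.375.
- Drop-out even over months 4–24: m = 0.5 × 0 + 0.5 × 0.5 = 0.25.

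| Drop-out timing | Relative shortfall, all randomised | All randomised | Known status | Completers |
|---|---|---|---|---|
| Before month 4 | 0.15 × 1 = 15% | 34.0% | 0.340/0.850 = 40.0% | 40% |
| Even, months 0–24 | 0.15 × 0.375 = 5.6% | 37.8% | 0.3775/0.8875 = 42.5% | 40% |
| Even, months 4–24 | 0.15 × 0.25 = 3.8% | 38.5% | 0.385/0.895 = 43.0% | 40% |

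**Other timings of change, all randomised.** If every change falls at month 4, the shortfall is 0.15 × 4/24 = 2.5% with drop-out even over 0–24 months and 0% with drop-out only after month 4. If changes are even over 4–24 months, it is 0.15 × 14/24 = 8.75% and 0.15 × 0.5 = 7.5% respectively. The shortfall dm does not depend on p.

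**What completers discard.** Changes seen in patients who later leave number 70 × dp(1 − m) per arm. With drop-out over months 4–24 this is 70 × 0.15 × 0.40 × 0.75 = 3.2, out of 70 × 0.385 = 27.0 changes seen.

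**Between arms, equal drop-out.** The ratio is unchanged and the difference is multiplied by (1 − dm). At m = 1, an assumed 20% v 40% becomes 17% v 34%, so 20 points become 17. Power at two-sided 0.05 with 70 per arm falls from 74% with complete follow-up to 64%. With 60 completers per arm it is 67%.

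**Between arms, unequal drop-out (illustration only).** If 10% v 20% left before month 4 with a true 40% in both arms, an all-randomised denominator would show 0.40 × 0.90 = 36% v 0.40 × 0.80 = 32%.

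**Kaplan-Meier.** Each patient contributes to the risk set until change or last contact. With drop-out unrelated to change, the estimate targets 40% in all three rows and uses every change that was seen.

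**The case against.** A reader might infer that the plan counts drop-outs as unchanged, so that each arm's percentage is about 15% too low. The documents do not support this. No denominator is stated. The intention-to-treat wording concerns the OSS analyses and the follow-up of patients who change; it does not assign a status to lost patients. A Chi-squared table needs a value only for the patients who are in it. The 15% is a sample-size allowance with no timing, and a missing 4-month score does not by itself leave treatment status unknown to month 24. These points stand.

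A reader might also infer an inflated type I error. That would need drop-out to differ between arms, and the article gives no sign of the size of any difference. Patients and assessors are blinded, and four of the six follow-ups are by e-mail with reminders. This stands too.

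It can further be said that all patients share a 24-month horizon, so a proportion is a legitimate summary; that a condensed article may leave the denominator to a fuller document; and that Kaplan-Meier also needs independent censoring. The last point is a real limit. If all 15% of drop-outs were unseen changers and the true rate were 40%, an all-randomised count would show 25%, a relative shortfall of 0.15/0.40 = 37.5%, and censoring at last contact would not fully repair it.

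The objection does not remove the narrower point. The measure and the kind of test are stated, and neither uses follow-up time. None of the three denominators is both free of bias, under drop-out unrelated to change, and able to use every observed change.

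**Conclusion.** The point holds as a minor improvement to one secondary outcome; it is not a demonstrated bias. With 15% drop-out unrelated to change, an all-randomised denominator lowers each arm's percentage by 0% to 15% in relative terms over the timings examined. It is about 4% to 6% when half of changes fall at month 4 and drop-out is late or even, and 15% only when all drop-outs leave before month 4. A known-status denominator can instead overstate, giving up to about 43% for a true 40%. Completers are unbiased under the same assumption but waste some observed changes. The change rate and all timings are assumptions, and a 24-month loss above 15% would raise the upper bound accordingly. Drop-out that differs between arms could distort the comparison, but its size cannot be judged from the documents. The primary outcome is not affected.

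**What to change.** Define the outcome as time from intervention to first change of treatment, counting the treatments listed under Change of treatment, including a repeat of the primary one. Censor at last contact or 24 months, whichever comes first. Report the Kaplan-Meier cumulative proportion with 95% CI per arm, and compare arms by a log-rank test stratified by hospital, which is the randomisation stratum. Keep the raw numbers per arm as a descriptive line, with their denominator stated.

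The cost is a few sentences in the outcome and analysis sections, plus the dates of change and of last contact. No extra visits or patients are needed. The remaining weakness is the assumption that, within an arm, drop-out is unrelated to later change. That is weaker than assuming that no lost patient changed, but it should be stated with the result.

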### Scoring instruments

All scoring instruments which will be used in the study are patient related outcome measures.

The OSS [14, 15] is a validated shoulder specific, 12-item score. It contains questions about pain and function and has been shown to be responsive to both surgical and non-surgical interventions on the shoulder. Its scoring method was modified in 2009 so that each of the 12 questions has five response categories scored from 4 (best) to 0 (worst) resulting in a total score ranging from 0 to 48 with a lower result indicating a greater degree of disability [15].

The QuickDASH upper extremity score [16, 17] is a shortened version of the DASH score with the number of items reduced from 30 to 11. It uses 5-point Likert scales to assess physical function and symptoms. It includes two domains for sport/art and work that are scored separately. The obtained value is transformed to a score ranging from 0 to 100 with a higher score indicating greater disability.

The Norwegian translation of the OSS and the Norwegian and Swedish version of the DASH score have been validated [23–25].

The EQ-5D-5L [18, 19] measures general health related quality of life. It comprises the dimensions mobility, self-care, usual activities, pain/discomfort, anxiety/depression each with 5 response categories, ranging from no problems to extreme problems. The score further includes a visual analogue scale for assessment of the health condition, ranging from the worst health (0) to the best health (100) you can imagine. Results can be presented as a health profile or as an index value.

Shoulder pain over the last week will be measured on three 0–10 visual analogue scales for pain at rest, during activities and at night. The scales are labelled no pain at the left end and worst imaginable pain at the right end.

The SETS [20] is a quick and easy-to-administer tool for the measurement of positive and negative pretreatment expectancies. The score consists of six items, three of them measuring positive expectancy, and three of them negative expectancy. It can be used to assess the influence of pretreatment expectancies on the outcomes in trials comparing real and sham treatment.

### Change of treatment

Patients who are still symptomatic or have redeveloped symptoms at four month follow-up or later, will be considered for supplementary treatment measures by the blinded follow-up assessor. If necessary, they will be offered treatment as usual, which means barbotage (repeated barbotage if barbotage was the primary treatment), steroid injection (repeated injection if injection was the primary treatment), ESWT, surgery, or therapist guided physiotherapy treatment, depending on findings and patient preferences. Earlier re-examination and change of treatment can be considered, in accordance with the Helsinki Declaration, for patients who are symptomatic to an extent that they cannot wait until the four month control. Patients who change the treatment during follow-up will remain in the study and will be followed-up according to an intention-to-treat principle. Unblinding of patients in conjunction with a change of treatment, will only be performed if the patient explicitly insists on knowing his primary treatment selection.

### Concomitant pain management

Previous treatment with analgesics is allowed but has to be stopped 48 h prior to baseline. In the post-treatment period the use of non-prescription analgesics such as Paracetamol (500 mg), Ibuprofen (600 mg) or Naproxen (250 mg) is permitted as it is considered part of the treatment. If post-treatment pain management necessitates the use of prescription analgesics the type and dosage will be recorded in the patients case report form at 4 and 24 month follow-ups.

### Harms

An adverse event diary will include all occurrences that the patient perceives as an adverse event. At follow-up, adverse events will be recorded by the follow-up assessor and will be sent to the sponsor. Once a year throughout the clinical trial, the sponsor will provide the respective Medicines Agency with an annual safety report. The format will comply with national requirements. If serious adverse events should occur, the sponsor will be informed immediately by phone or email.

### Sample size

Calculation of sample size was performed for an ANOVA of our primary outcome, which is the result on the OSS at 4 month follow-up. To detect a minimally important difference of 4 (SD 7) points [26] with a power of 90%, a 2-sided significance level of 0.05, 60 patients are required in each treatment group. To compensate for expected 15% drop-outs, we plan to include 70 patients in each treatment group. A supplementary analysis showed that this sample size also will be sufficient for pairwise post hoc *t*-test analyses (1 versus 2, 2 versus 3 and 1 versus 3), still with a significance level after Bonferroni correction of 0.017 but with a power of approximately 80%.

The actual statistical analysis of the interventions on primary outcome will be conducted using linear mixed models for repeated measurements adjusted for outcome measure at baseline. It is expected to give a slightly higher statistical power than an ANOVA.

### Statistical analysis

Demographic baseline data will be expressed for categorical variables as number of cases and for continuous variables by means with SD (if normally distributed) or by medians with range (if not normally distributed).

A linear mixed model for repeated measurements will be used for analysis. Because of an expected large number of crossovers after 4 months, the primary analysis will be performed on results up to 4 month follow-up and a secondary analysis on results up to 24 month follow-up. Analyses will be performed adjusted for baseline differences of the OSS and according to intention-to-treat. The linear mixed model will be estimated using linear maximum likelihood and include a random intercept, measure of the OSS at baseline as a covariate and observation time after intervention and type of intervention as factors. Mean differences (95% CI) between groups at 4 months follow-up will be presented from the linear mixed model to assess difference between interventions. A 2-sided *p*-value ≤ 0.05 is considered significant. Post-hoc pairwise comparisons for the primary outcome will be performed with p-value adjustments according to Bonferroni. Missing values will be handled by using mixed model analysis. Supplementary per-protocol analyses will be performed. A similar statistical analysis as described for the OSS will be used for the continuous secondary outcomes (QuickDASH, EQ-5D-5L).

Categorical variables will be expressed as numbers and percentages, and differences between groups will be analysed by the Chi^2^ or Fisher’s exact test. Possible associations between categorical baseline variables and outcomes will be explored by logistic regression analysis.

All subgroup analyses will be exploratory in nature and are planned for the size of the calcification at baseline (≤12.5 mm versus >12.5 mm), the volume of the removed material (≤0.1 ml versus > 0.1 ml), and the results on the Stanford expectation of treatment scale (positive expectancies versus negative expectancies). Selection of the threshold values for the size of the calcification at baseline and for the volume of the removed material are based on the findings of an unpublished pilot study from our institution.

Clinical safety will be investigated by assessing adverse events in a descriptive manner.

The statistician responsible for data analyses will blinded from the treatment allocation until completion of analyses.

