## Methods/Design

### Trial design

The study will be performed at five hospitals in Norway and one hospital in Sweden as a pragmatic, randomized, three-arm, parallel group, double-blinded, sham-controlled superiority trial with a 2-year follow-up (Fig. 1). Departments of orthopaedics, radiology and physical medicine and rehabilitation will be involved in the conduction of the study. The recruiting sites are Martina Hansens Hospital, Sandvika; Helse Fonna Hospital, Stord; Haraldsplass Deaconess Hospital, Bergen; Vestfold Hospital, Stavern; Oslo University Hospital, Oslo; (all Norway), and Linköping University Hospital, Linköping, (Sweden). The population group that will be considered for study participation consists of patients referred from general practitioners from the catchment areas of the study hospitals. They represent the unselected group of patients with painful calcific tendinitis with inadequate effect from treatment measures performed in general practice care. Patients who will have to be excluded according to the criteria given in Tables 1 and 2 will be reported. Inclusion, treatment and follow-up of study patients will be performed by hospital based physicians, specialised in physical medicine or orthopaedic surgery, all with long experience and special interest in the treatment of shoulder patients. At one site the study intervention will be given by a radiologist. The study hospitals represent different types of hospitals ranging from university hospitals to municipal hospitals and from hospitals with an urban to those with a rural location. Study medication and equipment is available at all study sites as all study interventions are part of already existing treatment routines. The study will be conducted in compliance with the principles of the Declaration of Helsinki, the principles of Good Clinical Practice (GCP) and under consideration of national laws and regulations, and will be reported in accordance with the CONSORT guidelines.

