### Randomisation

Patients who fulfil the inclusion and exclusion criteria and who have signed the consent form after oral and written study information was given, will be randomized to one of the three treatment options. Randomization will take place on the day of the intervention by an online central randomization system (web-CRF) developed and administered by the Unit of Applied Cancer Research, Institute of Cancer Research and Molecular Medicine, Norwegian University of Science and Technology, Trondheim, Norway. To assure verifiability of the randomization, patient initials, year of birth and name of the treating hospital will have to be registered at the central randomisation database. After registration, the intervention group for the specific patient will be displayed on-screen. Allocation will be 1:1:1. Block randomization with varying block lengths and stratification according to hospital will be performed. The randomisation list will remain at the University of Trondheim for the whole duration of the study and, consequently, will be inaccessible for the investigators, care providers and outcome assessors at the study centres.

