### Intervention

An orthopaedic surgeon (2 hospitals), a radiologist (1 hospital), or a specialist in physical medicine (3 hospitals), all with at least 5 years of experience in diagnostic and interventional ultrasound of the shoulder will conduct the allocated interventions. To ensure consistency a video of the procedure was produced and send to all trial sites (Additional file 1: Video barbotage procedure).

Interventions will be performed with the patient in supine position. The arm will be internally rotated to a degree that the treating physician considers to be the most favourable for the puncturing of the calcific deposit (usually arm on the back). An opaque sheet will be used to block the patient’s view of the screen of the ultrasound machine. After sterile skin preparation, with a 7 to 14 MHz transducer wrapped in a sterile drape, and by using sterile jelly, the calcific deposit will be sonographically identified, usually on the lateral transversal view. A 21-gauge needle will be introduced into the shoulder under sonographic guidance, and the pathway and the subacromial-subdeltoid bursa will be anesthetized with an injection of 10 ml of 1% lidocaine hydrochloride with adrenaline 5 μg/ml.

In patients randomized to barbotage a new 18-gauge needle connected to a 5 ml syringe with 4 ml of saline solution will be used to puncture the calcification using freehand technique under continuous sonographic monitoring. With the tip of the needle placed in the centre of the deposit, the calcification will be flushed. If backflow of calcific material can be identified in the syringe, lavage of the deposit will be performed by successive propulsion and aspiration with the syringe plunger. Extracted calcium can be visualized in the syringe as a cloudlike substance that settles at the bottom of the barrel. To avoid reinjection of the calcium into the deposit, the needle and the syringe will be hold in the horizontal plane during the procedure. The syringe will be substituted when the fluid has become cloudy and the procedure will be repeated until the backflow becomes clear. At the end of the procedure the content of the syringes will be poured into a measuring cup and, when settled at the bottom of the cup, the volume of the extracted calcium will be estimated. In cases where no material can be extracted, repeated perforation of the deposit will be performed to possibly initiate or accelerate spontaneous resorption.

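### Randomisation is stratified by hospital but the primary model omits hospital; if hospital predicts the OSS after baseline adjustment, some precision is lost

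*Protocol article*

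**What the plan says.** The Randomisation section of the protocol article sets the design: "Block randomization with varying block lengths and stratification according to hospital will be performed", and "Allocation will be 1:1:1". Hospital is the only stratification factor named. The Trial design section gives six strata: "The study will be performed at five hospitals in Norway and one hospital in Sweden".

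The Statistical analysis section specifies the primary mixed model. It will "include a random intercept, measure of the OSS at baseline as a covariate and observation time after intervention and type of intervention as factors". The same section states that "Analyses will be performed adjusted for baseline differences of the OSS and according to intention-to-treat", and the Sample size section likewise speaks of "linear mixed models for repeated measurements adjusted for outcome measure at baseline". Baseline OSS is therefore the only adjustment named, and no other part of the article adds hospital or centre to an analysis. The level of the random intercept is not stated; in a repeated-measures model it is naturally the patient.

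**The concern.** Blocked randomisation within hospital balances the arms at each site, so differences between hospitals in mean OSS largely cancel from the comparison of arms. The true sampling variance of the treatment difference is reduced accordingly. A model without hospital does not know this. It leaves the between-hospital variation in its error or patient-intercept variance and reports a standard error that is too large. Confidence intervals are then too wide and tests reject too rarely under the null hypothesis.

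The article gives some reasons to think hospital could be prognostic. The sites are in two countries, use two questionnaire languages, and range from university to municipal and from urban to rural. The operator's specialty also varies by site: "An orthopaedic surgeon (2 hospitals), a radiologist (1 hospital), or a specialist in physical medicine (3 hospitals").

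What is at stake is precision, mainly in the pairwise comparisons, where the Sample size section itself claims only about 80% power.

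**Working it through.** **Inputs from the Sample size section.** "To detect a minimally important difference of 4 (SD 7) points"; 60 evaluable patients per arm and 70 after allowing for drop-out; two-sided level 0.05 overall and 0.017 for each pair; power 90% overall and about 80% pairwise.

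**Assumption.** ICC is the share of OSS variance that lies between hospitals. The article does not give it; the range 0 to 0.10 is used.

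**Step 1: the plan's own figures.** One-way ANOVA, three groups, means (0, 0, 4), SD 7, n = 60 per arm. The grand mean is 1.333, so the noncentrality is 60 × (2 × 1.333² + 2.667²) / 49 = 60 × 10.667 / 49 = 13.06. Power is 90.4%, so the stated 60 per arm reproduces. Pairwise power at 0.017 is 76.0% (t-test) or 77.1% (normal approximation) at 60 per arm, and 83.1% or 84.0% at 70 per arm. The stated figure of about 80% lies between these. None of these calculations uses hospital.

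**Step 2: standard errors.** Total SD is held at 7.
- Without hospital: SE = 7 × √(2/60) = 1.278.
- With hospital, which is also the true sampling SD under balanced strata: SE = 7 × √(1 − ICC) × √(2/60).
- Ratio R = 1/√(1 − ICC).

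**Step 3: actual level and power (normal approximation).** Let c = 2.387, the critical value at two-sided 0.017, and let SE_h be the SE with hospital.
- Actual level of a nominal 0.05 test without hospital: 2 × [1 − Φ(1.96 × R)].
- Power without hospital: Φ(4/SE_h − c × R).
- Power with hospital: Φ(4/SE_h − c).

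At ICC 0.05: 4/1.246 = 3.211. Without hospital, Φ(3.211 − 2.387 × 1.026) = Φ(0.762) = 77.7%. With hospital, Φ(3.211 − 2.387) = Φ(0.824) = 79.5%.

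**Step 4: equivalent sample size.** Find the n at which the test without hospital reaches the power of the test with hospital at 60 per arm: n/60 = [1 + c(R − 1) / (4/SE_h)]².
- ICC 0.05: (1 + 0.0620/3.211)² = 1.039.
- ICC 0.10: (1 + 0.1291/3.299)² = 1.080.

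| ICC | SE with hospital | SE too wide by | Actual level, nominal 0.05 | Power without → with hospital | Equivalent extra patients |
|---|---|---|---|---|---|
| 0 | 1.278 | 0% | 0.050 | 77.1 → 77.1% | 0% |
| 0.01 | 1.272 | 0.5% | 0.049 | 77.2 → 77.6% | 0.8% |
| 0.02 | 1.265 | 1.0% | 0.048 | 77.4 → 78.1% | 1.5% |
| 0.05 | 1.246 | 2.6% | 0.044 | 77.7 → 79.5% | 3.9% |
| 0.10 | 1.212 | 5.4% | 0.039 | 78.3 → 81.9% | 8.0% |

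**Step 5: simulation check.** Six hospitals, 10 patients per arm per hospital, 20,000 runs, t-tests at 0.05/3. Pairwise power without → with hospital was 76.5 → 76.5% (ICC 0), 76.9 → 78.6% (0.05) and 77.8 → 81.0% (0.10). Under the null at ICC 0.05, the test without hospital rejected in 1.36% of runs against a nominal 1.67%. Levels are about one point below the normal approximation, but the gains agree to within half a point. At ICC 0 the extra term cost no power.

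Both calculations treat the 4-month OSS as a single measurement with no baseline adjustment, so they indicate size only and do not reproduce the planned mixed model.

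**The case against.** The strongest counter-argument is that the loss may be close to nil. The article gives no ICC, and what matters is the share left after adjustment for baseline OSS, which may already absorb differences in case mix. Outcomes are patient-reported and entered digitally, all operators have at least 5 years of experience and share a procedure video, and the exercise programme is standardised and home-based. All of this could keep the share low, and at ICC 0.01 to 0.02 the gain is below one point of power. This stands: the consequence is conditional.

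Operator specialty is also weak support. Differences in barbotage skill would act mainly as a treatment-by-hospital difference, which a main effect for hospital does not address.

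A reader might infer more than the article supports in four ways:
- That the result is biased or produces too many false positives. It does not; the error is on the conservative side.
- That the stated 90% power fails. It was computed without hospital and reproduces at 90.4%. What is lost is extra precision that the plan never counted on.
- That the loss equals 1/(1 − ICC), or 5.3% and 11.1% more patients at ICC 0.05 and 0.10. That overstates it: the test without hospital already benefits from the balanced allocation and loses only through its oversized standard error, which gives 3.9% and 8.0%.
- That hospital is covered because the random intercept could be for hospital. The model would then not handle repeated measurements within patients, so this reading is unlikely.

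Nor is this a detail merely left to a separate analysis plan. The article names the covariate, the factors and the random effect, so a plan that follows it would omit hospital.

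**Conclusion.** The point holds as a modest matter of efficiency. The listed model does not match the stratified randomisation. If hospital predicts the OSS after baseline adjustment, intervals are somewhat too wide and power is lower than the design allows. Over the assumed ICC range of 0 to 0.10, the standard error is 0 to 5.4% too wide and the pairwise power forgone runs from 0 to 3 or 4 points. That the term is missing is certain from the text; the size is not, because it rests on an assumed ICC, a total SD of 7, 60 evaluable patients per arm, near-equal balance within hospitals, and no credit for baseline adjustment. The validity of the primary comparison and the sample size justification are not in question.

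**What to change.** Add hospital as a fixed effect with six levels to the primary mixed model, and to the corresponding models for the continuous secondary scores. State at the same time that the random intercept is for the patient. Specify this before unblinding, so that the adjustment cannot be seen as chosen from the results. The cost is 5 degrees of freedom against about 180 evaluable patients (3 × 60). No new data are needed, since hospital is already recorded at randomisation, and no change to the sample size is required.
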